[21]. In a recent study, only a third of patients with COPD and clinically significant depression or anxiety were being treated and only half of those with severe depression or anxiety were being treated
[22]. Antidepressants can significantly improve mood among patients with COPD and depression
[23].

One reason these patients may receive poor-quality palliative care is that patient–physician communication about end-of-life care often occurs late in the illness
[24,25]. Healthcare for these patients is often initiated in response to acute exacerbations rather than being initiated proactively based on a previously developed plan for managing their disease
[26].

Studies have shown that only a minority of patients with moderate-to-severe COPD has discussed treatment preferences and end-of-life care issues with their physicians and most believe that their physicians do not know their preferences for end-of-life care
[24,25,27]. A survey of 214 general practitioners in the UK found that, although 82% felt that general practitioners should discuss prognosis with COPD patients, only 41% reported "often" or "always" discussing prognosis with these patients
[28]. Furthermore, two thirds of the physicians who reported infrequently discussing end-of-life care reported feeling inadequately prepared to have such discussions.

The "SUPPORT" study (study to understand prognosis and preferences for outcomes and treatment) that/which enrolled seriously ill hospitalized patients, including COPD, demonstrated that COPD compared to patients with lung cancer, were much more likely to die in the intensive care unit, on mechanical ventilation and with dyspnea
[29]. These differences occurred despite most patients with COPD preferred treatment focused on comfort rather than on prolonging life. In fact, SUPPORT found that patients with lung cancer and patients with COPD were equally likely to prefer not to be intubated and not to receive cardiopulmonary resuscitation (CPR), yet patients with COPD were much more likely to receive these therapies
[29]. A study of patients with COPD or lung cancer in the US Veterans Affairs Health System also found that patients with COPD were much more likely to be admitted to an ICU, and have greater lengths of stay in the ICU during their terminal hospitalization, than patients with lung cancer
[30].

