The primary objective of the study is to assess the effectiveness of the introduction of early specialized palliative care on hospital, intensive care unit and emergency admissions of patients with severe and very severe COPD.

The secondary objectives are to assess impact of early palliative care on:

1. mood and anxiety of patients with severe and very severe COPD

2. health-related quality of life of patients with severe and very severe COPD.

3. pattern of antibiotics used during the last month of life

4. advance care planning and end-of-life decision-making

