	- Assessment of symptoms with the Edmonton Symptom Assessment Scale
	- If intensity of pain, dyspnea, mood, anxiety and appetite >4 and patient agrees: patients will be referred to home based specialist palliative care team or another specialist (dieticians, pulmonologist, psychiatrist…)
	- Symptom management will follow the palliative care guidelines of the University Hospital of Geneva.
	- Non pharmacological interventions such as relaxation will be promoted according to Booth [42]
2.	**Understanding of illness and coping with the disease:**
	**-** History of disease made with the patient
	**-** Experience of patient with breathlessness
	**-** Information about dyspnea and the disease (discussion and booklet)
	**-** Information about morphine if needed (discussion and booklet)
3.	**Anticipation**
	**-** Values of the patients (what is important for you)
	**-** Patient preferences for end-of-life care: hospitalization f.ex
	**-** Information about advance directives, nomination of surrogate decision maker (booklet and discussion)
4.	**Relatives support**
	**-** Identification of the most important relative
	**-** Assessment of their needs
	**-** Provision of available resources
5.	**Social support**
	**-** Assessment of needs (financial, administrative.)
	**-** Provision of available resources
6.	**Spiritual support**
	**-** Assessment of needs
	**-** Provision of avalables ressources
7.	**Coordination of the health professionals**
	**-** Listing of the health professionals involved in the situation
	**-** Discussion with them of goals of care

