### Outcomes measures

Regarding the primary outcome, Hospital, ICU and emergency admissions will be collected in both groups form the medical records once a month. Length of stay in the different divisions, type of divisions (i.e.: internal medicine, rehabilitation) and reasons for admissions will be collected.

Regarding the secondary outcomes of the study:

– Mood and anxiety of patients will be measured with the self-assessment instrument: the Hospital Anxiety and Depression Scale (HADS)
[50,51]

– Quality of life will be measured with the SF-36 short form: a self-assessment scale validated in this population, and the COPD Assessment Test (CAT): a short, simple instrument for quantifying the symptom burden of COPD in routine practice

– Use of antibiotics during the last three months will be recorded

– Completion of advance directives, documented preferences for resuscitation, or nomination of surrogate decision maker will also be recorded

The secondary outcomes will be collected at baseline and at weeks 12, 24, 36 and 48.

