### Data collection

Baseline data will be collected in each patient’s home by the study nurse. The timing of interventions and data collection has been designed to not be too burdensome in this population with a severe disease
[15].

The baseline characteristics of the participants that will be measured are:

– Socio-demographic items: age, sex, marital status, education, children, living condition

– Smoking habits, weight, height, co-morbidities measured by the CIRS
[52], activities of daily living
[53], artificial nutrition (enteral, parenteral), prescribed treatment

– health professionals who participated to their care over the past three months (ie: nurses , dietician, occupational therapist)

– Additional equipment such as electric bed, wheelchair

– Characteristics and management of COPD: pulmonary function tests, oxygen saturation, use of oxygenotherapy, use of NIV, pharmacological treatment, numbers of acute exacerbations, admissions to emergency room, intensive care unit and hospital over the past three months Location and date of death will be collected from the medical records

Most of these data will be collected during the collection of primary and secondary outcomes (at weeks 12, 24, 36 and 48).

Data will be collected in computer files and will be rendered anonymous, without any reference to initials. Only the principle investigator will have the key to the correspondence between patient reference number and identity. The CRF (case report form) will be collected using SecuTrial software with the support of the Clinical Research Center, Geneva University Hospitals ([name]). A clinical research fellow, allocated for this project will adapt the data base and enter the data in the SecuTrial software.

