### Power calculation

One hundred-thirteen patients are currently followed by the Division of Pulmonary Disease in the University Hospital Geneva because of treatment with NIV and/or LTOT. We know that between one third and one half of these patients are hospitalized at least once during the year. Furthermore approximately 200 COPD patients per year are admitted to the Emergency Division of our hospital. Even if only a third of these patients are included in the study, this would give us sufficient statistical power to validly analyze our primary outcomes. Regarding the primary outcome, we calculated that a sample size of 80 patients per group would be adequate with an 80% power to detect a difference in hospital admissions of 20% between both groups at an α significance level (2-sided test) of 0.05.

With regard to missing data, we will use the conservative approach of carrying the last observation forward for all missing data in the intention-to-treat analyses. Poisson or binomial negative regression models will be used to compare count data between the groups while adjusting for potential confounder. The trend in the evolution of the different scores will be assessed using mixed linear regression models.

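### Advance care planning is tied to 12-weekly collection with carry-forward and no stated capture at death, so planning documented shortly before death may be under-counted

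*Protocol article*

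**What the plan says.** The last of the four secondary objectives at the end of the Background section is the effect on "advance care planning and end-of-life decision-making". The Outcomes measures section gives the matching outcome: "Completion of advance directives, documented preferences for resuscitation, or nomination of surrogate decision maker will also be recorded". The same section then sets the timing for all secondary outcomes: "The secondary outcomes will be collected at baseline and at weeks 12, 24, 36 and 48".

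Two other extractions are described. For the primary outcome, "Hospital, ICU and emergency admissions will be collected in both groups form the medical records once a month" (Outcomes measures). For patients who die, "Location and date of death will be collected from the medical records" (Data collection). Neither sentence mentions advance care planning.

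On missing values, the Power calculation section says "we will use the conservative approach of carrying the last observation forward for all missing data in the intention-to-treat analyses". It makes no exception for death or for this outcome.

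**The concern.** The objective concerns decisions near the end of life, but the stated collection times stop at the last one that the patient reaches alive. If a resuscitation preference or surrogate is first documented after that point, the stated schedule does not pick it up, and carry-forward then fills the gap with no planning documented. Within an arm the error runs one way: documentation already recorded is kept, and documentation added later is lost.

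The between-arm comparison is distorted only if this happens more often in one arm. The article gives a reason to expect that. Its Background says that patient–physician "communication about end-of-life care often occurs late in the illness", which describes usual care. The intervention puts the same subjects into its core content (Table 1: "Information about advance directives, nomination of surrogate decision maker (booklet and discussion"), delivered by a nurse who first sees the patient in the three weeks after inclusion and then every month or more often. At stake are the estimate for this objective and what it says about the patients who die, for whom the objective matters most. The primary outcome is not affected.

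**Working it through.** The article gives no rate, effect size or power for this outcome, so there is no figure of its own to reproduce. The calculation below is an illustration.

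**Age of the last recorded status.** Collections are 12 weeks apart, so a patient who dies before week 48 has a last status 0 to 12 weeks old. The mean is about 6 weeks if deaths fall evenly within intervals.

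**Share dying by week 48 (D).** Input: two-year mortality m of 36–50% after an exacerbation admission (Background). Assumption: constant hazard, with two years taken as 104 weeks.

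D = 1 − (1 − m)^(48/104)

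- m = 0.36: D = 1 − 0.64^0.4615 = 18.6%, or 0.186 × 80 = 14.9 deaths per 80 patients
- m = 0.50: D = 1 − 0.50^0.4615 = 27.4%, or 0.274 × 80 = 21.9 deaths per 80 patients

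The Power calculation section gives 80 per group and the abstract 90. With 90, the counts are 16.8 and 24.6. The percentages do not change.

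**Net bias.** Let qC and qI be the shares of control and intervention deaths whose first documentation falls after the last collection and is not retrieved. Each arm's proportion is understated by D × q. With equal mortality in the arms, the difference (intervention minus control) is shifted by

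D × (qC − qI)

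The documents give neither share. All values of q below are assumed.

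| qC | qI | Shift at D = 18.6% | Shift at D = 27.4% |
|---|---|---|---|
| 30% | 30% | 0 | 0 |
| 30% | 10% | +3.7 points | +5.5 points |
| 50% | 10% | +7.4 points | +11.0 points |
| 10% | 30% | −3.7 points | −5.5 points |

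For example, in the second row at D = 18.6%, 14.9 × 0.30 = 4.5 control and 14.9 × 0.10 = 1.5 intervention patients per 80 are misclassified: (4.5 − 1.5)/80 = 3.7 points. A positive sign favours the intervention. For scale, the communication trial cited in the Background found 30% v 11% for end-of-life discussions, a gap of 19 points.

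**The case against.** The strongest reply is that a collection date does not limit the period it covers. Questionnaires need a living respondent, but directives and resuscitation preferences are documents that can be read back later. The antibiotic item beside them already looks back three months, about one collection interval. Records are opened monthly in both arms, and again to establish where and when a patient died. The source, look-back and death-form fields may well be in the full protocol or case report form. This stands in part: if records are searched to the date of death, the loss is zero. The point therefore rests on what the article does state, a fixed schedule joined to carry-forward for all missing data.

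The second reply concerns direction, and it stands. The article deliberately leaves the order of intervention topics open, so planning may come late in that arm too. Control patients can meet the palliative team on request. Late in the illness need not mean the last 12 weeks of life. The Background sentence about exacerbations concerns healthcare in general, not conversations about preferences, and cannot be used to time them.

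Third, for a trial of early palliative care, planning in place at fixed times is a legitimate outcome, and orders written in the last days are not the same thing. That is a reason to report both, not to leave one unrecorded.

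**Conclusion.** The point holds as a weakness in how the outcome is collected and filled in. Followed as written, the schedule and the carry-forward rule can score a patient as having no planning when it was documented before death. The word conservative in the missing-data rule is not justified for this outcome.

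A reader might infer more: that late decisions are never captured, that the loss falls mainly on controls, and that the result is therefore biased towards the intervention. The documents do not support this. They do not exclude reading records back, and they give no split of the loss between arms. A reader might also put the bias at 4–16 points by assuming that 20–60% of control deaths are affected (0.186 × 0.20 = 3.7 points; 0.274 × 0.60 = 16.4 points). That is the gross understatement in the control arm. It equals the bias only if the intervention arm loses nobody.

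What can be said is that the net bias is D × (qC − qI), with D at 18.6–27.4% under a constant hazard and equal mortality in the arms. A larger control share is plausible, but size and sign remain open. D itself may be too high, because the mortality figure applies after an exacerbation admission and patients can also enter on lung function or home treatment alone. This is a low-cost improvement to a secondary objective.

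**What to change.** - Keep the collection at weeks 12, 24, 36 and 48. In addition, abstract directives, resuscitation preferences and surrogate nomination, each with its date, from the medical records at the existing monthly review and once more when the death data are extracted.
- Do this identically in both arms, with an abstractor blinded to allocation where possible.
- Do not carry the last observation forward for this outcome in patients who die. Analyse it as documented by death or by end of follow-up, whichever comes first.
- Use the dates to report status at the fixed time points and status at death separately, so that early planning can be told apart from orders written in the last days.
- If the full protocol already requires a search of the records to the date of death, state the source and look-back, and exempt this outcome from the carry-forward rule.

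Cost: three dated fields in an extraction that is already planned, slightly more abstraction time, and no extra visit. The between-arm difference may look smaller.

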### Data collection

Baseline data will be collected in each patient’s home by the study nurse. The timing of interventions and data collection has been designed to not be too burdensome in this population with a severe disease
[15].

The baseline characteristics of the participants that will be measured are:

– Socio-demographic items: age, sex, marital status, education, children, living condition

– Smoking habits, weight, height, co-morbidities measured by the CIRS
[52], activities of daily living
[53], artificial nutrition (enteral, parenteral), prescribed treatment

– health professionals who participated to their care over the past three months (ie: nurses , dietician, occupational therapist)

– Additional equipment such as electric bed, wheelchair

– Characteristics and management of COPD: pulmonary function tests, oxygen saturation, use of oxygenotherapy, use of NIV, pharmacological treatment, numbers of acute exacerbations, admissions to emergency room, intensive care unit and hospital over the past three months Location and date of death will be collected from the medical records

Most of these data will be collected during the collection of primary and secondary outcomes (at weeks 12, 24, 36 and 48).

Data will be collected in computer files and will be rendered anonymous, without any reference to initials. Only the principle investigator will have the key to the correspondence between patient reference number and identity. The CRF (case report form) will be collected using SecuTrial software with the support of the Clinical Research Center, Geneva University Hospitals ([name]). A clinical research fellow, allocated for this project will adapt the data base and enter the data in the SecuTrial software.

### Statistics

To compare baseline characteristics and study outcomes of the patients between groups, Fishers’ exact tests, chi-square tests and the independent-samples t-test or the non-parametric equivalent Mann–Whitney u test will be used.

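### For HADS, SF-36 and CAT, make a baseline-adjusted mixed model on observed scores the main comparison, instead of two-sample tests with no stated baseline term and carried-forward values

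*Protocol article*

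**What the plan says.** Three parts of the protocol article bear on the score outcomes.

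- **Outcomes measures.** Mood and anxiety are measured with HADS. "Quality of life will be measured with the SF-36 short form", together with CAT. On timing: "The secondary outcomes will be collected at baseline and at weeks 12, 24, 36 and 48". Each score therefore has a baseline value and up to four follow-up values. These instruments serve two of the four secondary objectives listed in the Background.
- **Statistics.** "To compare baseline characteristics and study outcomes of the patients between groups", the section names Fisher's exact and chi-square tests, and for continuous or ordinal data the "independent-samples t-test or the non-parametric equivalent Mann–Whitney u test will be used". No outcome is excepted. Nothing says whether the tests use follow-up values or changes from baseline.
- **Power calculation.** "The trend in the evolution of the different scores will be assessed using mixed linear regression models". The same section names Poisson or negative binomial regression to "compare count data between the groups while adjusting for potential confounder", which is the only mention of covariate adjustment. It also commits to "carrying the last observation forward for all missing data in the intention-to-treat analyses".

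**The concern.** Taken as written, each score has two assigned analyses: a two-sample test with no stated baseline term, and a mixed model for trend. The baseline score is recorded before randomisation and is likely to be a strong predictor of the later score. A comparison of follow-up values that leaves it out gives a wider confidence interval and lower power from the same patients.

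The missing-data rule makes no exception for the mixed models. A mixed model does not need a complete set of visits, so it can use the scores actually observed. Carrying the last score forward replaces each later missing value with a flat line and treats it as measured. The Background describes progressive deterioration in these patients, so a flat line is a doubtful guess, and it enters directly into an analysis whose subject is the course of the scores over time.

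At stake is how well the trial can answer its questions on mood, anxiety and quality of life. The primary outcome is not affected by this point.

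**Working it through.** **The plan's own figure.** No sample size, power or effect size is given for HADS, SF-36 or CAT. The stated 80 per group refers to hospital admissions. Reading the 20% as an absolute difference, 40% vs 20% needs 82 per group and 38% vs 18% needs 78, so that figure can be recovered. It says nothing about the scores.

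**Inputs.**
- Two-sided α = 0.05 and 80% power, from Power calculation (there for the primary outcome, used here as the reference): z = 1.960 + 0.842 = 2.802.
- 80 per group from Power calculation. The Abstract gives 90; the ratios and the power column below do not depend on this number.
- Correlation ρ between baseline and follow-up score: **an assumption**, ranged over 0.3 to 0.7.

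**Formulas**, for one follow-up visit, with the score scaled to SD 1:
- variance with baseline adjustment, relative to follow-up values alone: 1 − ρ²
- variance ratio, unadjusted to adjusted (also the sample-size ratio): 1/(1 − ρ²)
- power of the unadjusted test for an effect with 80% power when adjusted: Φ(2.802·√(1 − ρ²) − 1.960)
- difference detectable with 80% power, 80 per group, adjusted: 2.802·√(2/80)·√(1 − ρ²) = 0.443·√(1 − ρ²) SD

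| ρ (assumed) | 1 − ρ² | Variance ratio | Power, unadjusted | Detectable, adjusted (unadjusted 0.44 SD) |
|---|---|---|---|---|
| 0.3 | 0.91 | 1.10 | 76% | 0.42 SD |
| 0.5 | 0.75 | 1.33 | 68% | 0.38 SD |
| 0.6 | 0.64 | 1.56 | 61% | 0.35 SD |
| 0.7 | 0.51 | 1.96 | 52% | 0.32 SD |

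Worked example at ρ = 0.7: 2.802 × √0.51 = 2.001; 2.001 − 1.960 = 0.041; Φ(0.041) = 0.52.

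**If the two-sample test uses change scores.** The document leaves this open. The variance of a change is 2(1 − ρ), that is 1.40, 1.00, 0.80 and 0.60 at the four correlations. Divided by 1 − ρ², this is 1.54, 1.33, 1.25 and 1.18 times the adjusted variance. A change score beats follow-up values alone only when ρ exceeds 0.5, and at each of these correlations it is less precise than adjustment.

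**The case against.** The strongest reply is that the Statistics sentence is a general list of simple tests that names no instrument, while the only sentence about scores assigns them to mixed models. On that reading the specific sentence governs. The two may also answer different questions: a difference at one visit, and the course over time. This limits the point. The general sentence still includes outcomes without exception, so the overlap is in the text, but it need not be a contradiction.

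It is also fair to say that a condensed article may leave the main analysis, target visit and model terms to a fuller document. Their absence alone is not a fault. What remains is what the article does state: two-sample tests with no baseline term for outcomes that have a baseline, and carried-forward values for all missing data.

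Two stronger readings are tempting, and the document supports neither.

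- A reader might infer that the plan as a whole throws away precision. It does not: the mixed model is also planned and can use the baseline score. The loss arises only if the two-sample test on follow-up values is what gets reported, and no section says so.
- A reader might infer that two analyses per score raise the false-positive rate from 5% to about 7 to 8%. That figure comes from pairing an unadjusted and a baseline-adjusted test at a single visit and counting either as positive. The article plans a trend model, not that second test, and does not say that either result may be claimed. The figure is not a property of the written plan.

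**Conclusion.** The point holds as a recommendation for a better method on secondary outcomes. The two-sample tests as stated carry no baseline adjustment. If they are applied to follow-up values and reported as the result, their variance is 1.1 to 2.0 times that of an adjusted comparison, and 80% power falls to about 76% to 52%. These figures rest on an assumed correlation of 0.3 to 0.7 and on a single-visit comparison. At the low end the loss is modest. If the mixed model with baseline is the reported analysis, this loss does not arise.

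The carried-forward rule is a separate weakness in the same analyses. It is stated for all missing data, so on its wording it reaches the mixed models, which do not need it. The document gives no expected amount of missing score data, so the size of that effect cannot be calculated.

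**What to change.** For HADS, SF-36 and CAT:

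1. State that the main between-group analysis is one mixed linear model of the follow-up scores, with treatment, visit, treatment-by-visit and the baseline score as covariate.
2. Name one treatment contrast in advance, for example the difference at week 48.
3. Fit the model to observed scores, and exempt these scores from the carried-forward rule.
4. In the Statistics section, limit the t-test and Mann–Whitney test to descriptive or supportive use for these scores.

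The cost is a few sentences of wording and slightly more analysis work. No extra visits, measurements or patients are needed. There is one trade-off to record: the model assumes that missing scores can be explained by the observed data, and a patient with no follow-up score adds nothing to it. Carrying forward would keep that patient in the analysis, but only by treating the baseline value as an outcome.
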